## Abstract

**Background:**

Indonesia has the second largest tuberculosis (TB) burden globally. Attempts to scale-up TB control efforts have focused on TB households. However, in most high burden settings, considerable *Mycobacterium tuberculosis (Mtb)* transmission occurs outside TB households. A better understanding of transmission dynamics in an urban setting in Indonesia will be crucial for the TB Control Program in scaling up efforts towards elimination of TB in a more targeted way. Therefore, the study aims to measure TB prevalence and incidence in household contacts and neighbourhoods in the vicinity of known TB cases and to assess their genomic and epidemiological relatedness.

**Methods and analysis:**

Individuals (~1000) living in the same household as a case diagnosed with pulmonary TB (n = 250) or in a neighbouring household (~4500 individuals) will be screened for TB symptoms and by chest x-ray. Two sputum samples will be collected for microbiological analysis from anyone with a productive cough. Any person found to have TB will be treated by the National TB Control Program. All those with no evidence of TB disease will have a repeat screen at 12 months. Whole-genome sequencing (WGS) and social network analysis (SNA) will be conducted on Index cases and contacts diagnosed with TB.

## Introduction

Tuberculosis (TB) remains a leading cause of infection globally, with an estimated 10 million new cases of disease and 1.2 million deaths from TB in 2019 [1]. To eliminate TB, we need to identify target populations most at risk so that enhanced intervention can drive the incidence of TB down across the wider population. Many attempts to intensify TB control efforts have focused on TB households [2–4]. However, we now know that in most high burden settings, the majority of *Mycobacterium tuberculosis (Mtb)* transmission occurs in the community where there are vastly greater numbers of human encounters [5] that often share socio-economic risk factors that are correlated with TB [6, 7]. In a feasibility study in Bandung, Indonesia [8] we followed individual TB patients back to their communities. We found an incidence rate of self-reported TB of 649 per 100,000/year in TB household contacts, 675 in neighbouring households, and 325 in randomly selected neighbourhoods [8].

TB disease occurs through two distinct mechanisms (primary progression and reactivation) that require different interventions. Soon after exposure to *Mtb*, a small proportion of people develop TB disease (primary progression) and approximately 50% of them are latently infected but remain well. Of these latently infected people, 5% develop TB disease during their lifetime (reactivation) [9–11]. Early diagnosis and six months of multi-drug treatment of TB disease reduces transmission to case contacts, and preventive treatment of latent TB for as little as three months reduces reactivation in infected contacts by up to 90% [12, 13]. Both strategies are essential for TB elimination [14]. If neighbourhoods around TB cases have high rates of TB, then this is likely to be due to a particular mix of primary progression and reactivation disease.

Indonesia has the second largest TB burden globally (prevalence estimate 647/100,000 population) [15]. Bandung City, in the province of West Java, has a population of approximately 2.4 million inhabitants. Much of the diagnosis and treatment of TB is carried out in Community Health Centres (CHCs) and public hospitals. Diagnosis by sputum microscopy and provision of anti-TB medication in these health facilities is provided free of charge by the National TB Program (NTP). Approximately 2200 sputum smear-positive TB patients are notified per year from the 80 CHCs located throughout the city (~28 TB patients per CHC), each of which have a defined catchment area.

We present a protocol of a study aimed to measure the TB prevalence and incidence in households and neighbourhoods of a known TB case. We also aim to assess how genomic and epidemiological relatedness varies between TB cases from household contacts, and those from the neighbourhoods.

## Methods

### Study design

The study will interlink with an ongoing randomised trial of an intervention to increase notifications of TB cases from private practitioners (PP) [16]. Thirty-six CHC areas in Bandung have been randomised 1:1 to receive a multi-component intervention with PPs or continue the standard practice. Our study will recruit participants from six of the intervention areas included in the trial selected to be in proximity to each other. The study consists of two main components: 1) a prospective cohort study; and 2) whole-genome sequencing (WGS) and social network analyses (SNA) (Fig 1).

**Fig 1 pone.0256043.g001:**
[figure not shown]
Overall study schematic.

#### 1) Prospective cohort study

*Study participation and recruitment*. From 250 bacteriologically-proven TB patients (Index case) living within one of the six selected CHC areas of Bandung City (as described above), we will conduct active case finding among household contacts (approximately four people per household) and neighbourhood members. Trained research staff will interview all persons aged 10 years and above living in the same household as the Index case, as well as all those living in the five houses closest to the Index case. We will record all subjects in the target households and assess their eligibility. We will not exclude any person with extra-pulmonary TB or being re-treated for TB for screening or follow-up. We will exclude any person in a household who normally lives at another location, or children under the age of 10 years.

The TB nurse in each recruitment site (CHC or hospital) will identify potential Index cases, ensure they are resident in the selected area and seek consent for their contact details to be forwarded for the study. Research staff will then contact consenting Index cases to arrange a time to visit them and their household when most household members are likely to be present. At the visit, further information will be provided and written informed consent obtained. The Index case will also be informed that we wish to contact neighbourhood households and their consent sought before proceeding. Research staff will identify five houses that are the closest in proximity from the Index case house. Within each identified neighbourhood household, the same procedure of informed consent will be followed. The research staff will be instructed not to reveal the identity of the Index case. Consent for any household members aged between 10 and 18 years will be sought from their parent or guardian.

*Data collection and screening algorithm*. For each Index case, socio-demographic information and results from their Acid-fast bacilli (AFB) smear and/or Xpert MTB/RIF testing at the CHC or hospital will be obtained. Sputum samples will be sent to the research laboratory for culture and storage. From each consenting household contact a symptom screen will be undertaken (Fig 2) as well as enquiry about any history of TB, whether they are on any TB preventive therapy, have any other immunocompromised medical condition, and their socio-demographic information (age, gender, ethnicity, smoking status). The location of each household will be recorded using an electronic geographic coordinate system. Any person with symptoms suggestive of TB (weight loss, night sweats, fever, chest discomfort or pain) will undergo clinical assessment. Any person with a productive cough of any duration will be asked to provide two sputum samples for AFB smear and/or Xpert MTB/RIF testing, and *Mtb* culture [17, 18]. All participants will be offered a chest x-ray, followed by sputum examination if the x-ray has changes suggestive of TB. Chest x-ray reports will be read by a radiologist. Cases with a radiology report showing indication of TB without bacteriology positivity will be consulted to an infectious disease specialist to determine whether they should receive TB treatment or not. All diagnostic procedures and treatment for any person found to have TB will be undertaken according to National TB guidelines.

**Fig 2 pone.0256043.g002:**
[figure not shown]
Baseline screening algorithm.

*Follow-up*. All participants with no evidence of TB at baseline will be contacted by phone approximately four-monthly to ask whether they have been diagnosed with TB in the interim. Also, to enable the study team to capture the sputum sample and obtain a culture at the time of diagnosis, household contacts will be given a referral card with the study contact details they can show to any CHC or hospital should they present with any TB symptoms or undergo any TB related diagnostic tests. At 12 months a repeat in-person symptom screen will be done (Fig 3). If an individual within a household leaves the neighbourhood area and cannot be followed-up, the approximate date they left will be ascertained from other household members. If a whole household leaves the area before the 12-month follow-up and are unable to be contacted, an approximate date will be confirmed from neighbours.

**Fig 3 pone.0256043.g003:**
[figure not shown]
Follow-up screening algorithm.

#### 2) Whole-genome sequencing and social network analysis

From each household contact who is diagnosed with TB, as well as Index cases, an interview will be undertaken using a social network questionnaire, and sputum cultured for Mtb will undergo WGS to ‘fine map’ their relatedness [19]. We will use the BWA-MEM algorithm to map the sequence data to the H37Rv reference genome. Variants will be called using Pilon (v1.22). We will assign a call as missing if the valid depth at a specific site is less than 12, if the mean read mapping quality at the site does not reach seven, or if none of the alternative alleles account for at least 85% of the valid coverage.

Pairwise genetic distances between each TB patient will be determined, after removing single-nucleotide polymorphisms (SNPs) in highly repetitive genes such as the PE/PPE genes and loci under strong selection. [20, 21]. For all pairs, we will obtain the shortest travel time between two points as an approximation of the geographic distance using Open Source Routing Machine, a publicly available tool that analyses Open Street Map road network data. We will assess the relationship between geographic and genetic distance across all pairwise samples to determine the relative contribution of close versus distant contacts in TB transmission. For five definitions of SNPs distances (0–1, 2–3, 4–5, 6–10, and 11–30 SNPs different), we will first compare the odds of genetic relatedness at each of the five levels among pairs within the household, pairs within the neighbourhood, and pairs from different neighbourhoods. We will repeat the same but classifying the pairs in to five categories (within the household, 0–5, 5–10, 10–20, and 20 or more minutes of travel time apart). We will also determine whether any of the household contacts share common meeting places such as employment venues, places of worship, markets, or restaurants.

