#### Genomic relatedness

We expect a maximum of 10% (95% CI 6.3–13.7%) of 250 community diagnosed Index TB cases will have an *Mtb* isolate that is genomically ‘identical’ to another Index case, compared to approximately 60% of Index TB case/household contact TB case pairs. Percentages for Index case/neighbourhood case pairs will lie between these values. Assuming we identify 35 culture-positive cases in contacts in 250 households and 75 culture-positive cases in neighbourhoods, we will have >95% power to detect significant differences (p = 0.05 level of significance), in percent genomically ‘identical’, for comparisons between community and Index TB case/household TB case pairs and between community and Index TB case/neighbourhood case pairs. We will also have over 80% power to detect a significant difference for a household versus neighbourhood comparison, if 60% or more of Index case/household case pairs are genomically ‘identical’ and 30% or less of Index case/neighbourhood case pairs are genomically ‘identical’.

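### The pairwise odds of genetic relatedness show how relatedness changes with distance; they do not give the relative contribution of close and distant contacts, which is their stated purpose

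*Protocol article*

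**What the plan says.** Section 2, Whole-genome sequencing and social network analysis, gives the purpose of the pairwise analysis: it works "across all pairwise samples to determine the relative contribution of close versus distant contacts in TB transmission". It then gives the measure. For five bands of SNP distance, "we will first compare the odds of genetic relatedness at each of the five levels among pairs within the household". The other two categories in that comparison are neighbourhood pairs and pairs drawn from separate neighbourhoods. The second analysis uses the same measure with travel time: "We will repeat the same but classifying the pairs in to five categories". The rest of that paragraph concerns shared meeting places. No share of linked cases or linked pairs by distance category is named.

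Three other places bear on this:

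- The Introduction says that most "transmission occurs in the community where there are vastly greater numbers of human encounters". It ends with the aim of assessing how genomic and epidemiological relatedness varies between household and neighbourhood cases.
- Sample size, Genomic relatedness, gives the expected rates: "We expect a maximum of 10% (95% CI 6.3–13.7%) of 250 community diagnosed Index TB cases" matching another Index case, "compared to approximately 60% of Index TB case/household contact TB case pairs", and for the household versus neighbourhood comparison "30% or less of Index case/neighbourhood case pairs are genomically" identical. The case numbers are there too: "Assuming we identify 35 culture-positive cases in contacts in 250 households and 75 culture-positive cases in neighbourhoods".
- The Discussion ties the choice of intervention partly to whether recent spread from Index households accounts for a large part of neighbourhood prevalence.

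**The concern.** Contribution is a share. For each distance category it is the probability that a pair is linked, multiplied by the number of pairs, divided by the total over categories. Odds within a category drop the number of pairs. That number is what the Introduction relies on when it explains why community transmission dominates.

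The categories differ enormously in size. A household contact case has essentially one household pair, with its Index case. The same case has hundreds of pairs with people in other neighbourhoods, nearly all of them unrelated even if one is its true source. Household odds can therefore far exceed distant odds both when close contacts account for most links and when they account for few.

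At stake is how the result is read. If a large household or neighbourhood odds ratio were reported as the relative contribution of close contacts, it could be taken to support targeting around Index cases in a setting where such contacts account for a small part of the links.

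**Working it through.** **Inputs** (Sample size, Genomic relatedness): 250 Index cases; 35 household and 75 neighbourhood culture-positive cases; 60% of Index/household pairs identical; 30% of Index/neighbourhood pairs identical (the upper value used for the household versus neighbourhood comparison); 10% of Index cases identical to another Index case.

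**The plan's own figure.** 0.10 ± 1.96 × √(0.10 × 0.90 / 250) = 0.10 ± 0.037, or 6.3% to 13.7%, as stated. The power statements also reproduce at these rates (pooled two-sided test at 0.05): above 99.9% for 60% v 10%, 97.4% for 30% v 10%, and 85.5% for 60% v 30%. They are not at issue here.

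**Pairs per category, all cases.**
- Total: 250 + 35 + 75 = 360 cases, so 360 × 359 / 2 = 64,620 pairs.
- Household: about 35, assuming one contact case per affected household.
- Neighbourhood: 75 with the Index case, plus about 35 × 75 / 250 = 10.5 between household contacts and neighbours, giving 85.5. Pairs of neighbourhood cases around the same Index case would add about (75 × 74 / 2) / 250 = 11, which changes nothing material.
- Different neighbourhoods: 64,620 − 35 − 85.5 = 64,499.5.

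**Linked close pairs.** Household: 0.60 × 35 = 21, odds 21/14 = 1.5. Neighbourhood: 0.30 × 75 = 22.5, odds 22.5/52.5 = 0.429. Together: 43.5.

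**Odds ratio by distant share.** Let s be the share of all linked pairs that are distant. The number of distant linked pairs is L = s/(1 − s) × 43.5, and the distant odds are L/(64,499.5 − L).

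| s (assumed) | L | Household OR | Neighbourhood OR |
|---|---|---|---|
| 50% | 43.5 | about 2,220 | about 635 |
| 80% | 174 | about 555 | about 158 |
| 90% | 391.5 | about 246 | about 70 |
| 95% | 826.5 | about 116 | about 33 |
| 99% | 4,306.5 | about 21 | about 6 |

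Example at 99%: 4,306.5/60,193 = 0.0715, and 1.5/0.0715 ≈ 21. The household odds ratio reaches 1 only when 0.60 × 64,499.5 ≈ 38,700 distant pairs are linked, a distant share of 38,700/(38,700 + 43.5) ≈ 99.9%.

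**At the plan's 10% Index matching, Index/Index pairs only.** There are 250 × 249 / 2 = 31,125 such pairs, and 25 matched cases. The linked pairs depend on how those cases cluster:
- All in twos: 12.5 pairs; distant odds 12.5/31,112.5 = 0.000402; OR 1.5/0.000402 ≈ 3,730.
- One cluster of 25: 25 × 24 / 2 = 300 pairs; distant odds 300/30,825 = 0.00973; OR ≈ 154.

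The same case-level figure thus gives odds ratios about 24-fold apart. This calculation treats all Index/Index pairs as lying in different neighbourhoods.

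**The case against.** The case on the other side is substantial.

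- *The study aim is met.* Relatedness by distance category is a proper answer to the aim that closes the Introduction. This stands. The mismatch lies only in the added claim about contribution.
- *The odds are not the whole genomic analysis.* The sample size section works with percentages, and the percentage of neighbourhood cases matching their own Index case is close to a case-level measure. In a strongly distant scenario that comparison would reverse. With 90% of Index cases linked to another Index case and 60% of household pairs matched, it sets 225/250 against 21/35: pooled proportion 246/285 = 0.863, standard error √(0.863 × 0.137 × (1/250 + 1/35)) = 0.062, z = 0.30/0.062 ≈ 4.8 in favour of the community. This stands too. A reader might infer that the genomic component cannot inform the programme at all; the document does not support that.
- *The counts are not lost.* Linked and total pairs in each category are needed to form the odds, so linked-pair shares can be recovered. True, but the article names no such step.
- *The article is condensed.* Further analyses may be in a fuller plan. If so, only the wording needs changing. Still, the article states both the purpose and the measure meant to serve it, and these do not fit. That is more than an omitted detail.
- *A closest-isolate table does not measure contribution exactly either.* Correct: it depends on who was sampled, and it must be presented that way.

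**Conclusion.** The point holds as a mismatch between a stated purpose and a stated measure. The pairwise odds describe how relatedness changes with distance. They do not determine the relative contribution of close and distant contacts, because they discard category sizes that differ several-hundred-fold. With household matching at 60% and neighbourhood matching at 30%, the household odds ratio is about 2,200 with half of the linked pairs distant and about 21 with 99% distant. It points the same way in both cases.

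The assumptions are one level of relatedness (identical), one contact case per affected household, and neighbourhoods that do not overlap. The distant shares in the table are illustrative and are not forecasts; any scenario with more Index matching than the plan's maximum of 10% is likewise hypothetical. Linked pairs are not transmissions: a cluster of 25 has 300 pairs but at most 24 transmissions among its members.

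Two stronger readings should be avoided. The odds ratio of about 3,730 is not the plan's implied value; it is the top of a range that falls to about 154, depending on clustering. Nor does this invalidate the genomic analysis, which still meets its relatedness aim.

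**What to change.** 1. Keep both sets of pairwise odds. Describe them only as the relation between genetic relatedness and distance, and remove relative contribution as their purpose.
2. From the same data, add a case-level table. For each sequenced case, find the closest other isolate within a SNP limit fixed in advance, and classify it as same household, same neighbourhood, different neighbourhood, or none within the limit. Fix a rule for ties in advance as well. Report percentages separately for household-contact, neighbourhood and Index cases, with confidence intervals from resampling Index clusters.
3. Present the table as descriptive and dependent on sampling. The different-neighbourhood share is likely understated, because households and the five nearest houses are actively screened while more distant cases are only partly sampled.

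The cost is one changed sentence and one extra table, with no new samples or participants. The downside is a weaker claim than the present wording makes.

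### The 0–5-minute travel-time band pools five-house neighbour pairs with other nearby pairs, so an excess confined to the five houses cannot be told from one that extends through the 5-minute radius

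*Protocol article*

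**What the plan says.** The protocol article, under 2) Whole-genome sequencing and social network analysis, sets out the pair analysis: "We will assess the relationship between geographic and genetic distance across all pairwise samples", with the purpose "to determine the relative contribution of close versus distant contacts in TB transmission". Relatedness is examined at five levels: "For five definitions of SNPs distances (0–1, 2–3, 4–5, 6–10, and 11–30 SNPs different".

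Two pair classifications are listed in full. The first compares odds of relatedness "among pairs within the household, pairs within the neighbourhood, and pairs from different neighbourhoods". The second repeats this after "classifying the pairs in to five categories (within the household, 0–5, 5–10, 10–20, and 20 or more minutes of travel time apart".

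Two design features decide who falls in the 0–5-minute band. Under 1) Prospective cohort study, neighbourhood contacts are defined by proximity: "as well as all those living in the five houses closest to the Index case". Under Study design, recruitment is from "six of the intervention areas included in the trial selected to be in proximity to each other".

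**The concern.** The second classification removes household pairs from the distance bands but leaves neighbourhood pairs in. The article does not state travel times for neighbours. But pairs drawn from an Index house and its five closest houses should lie almost entirely within 5 minutes. They share that band with every different-neighbourhood pair living that close, and such pairs are likely because the six areas were chosen to be near one another.

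Set side by side, the two analyses leave a gap:

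| Contrast | First classification | Second classification |
|---|---|---|
| Same five-house neighbourhood, kept apart | yes | no, merged into 0–5 min |
| Different-neighbourhood pairs split by distance | no | yes, but 0–5 min also holds neighbours |
| Same neighbourhood against pairs just beyond it | no | no |

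At stake is the meaning of a raised odds ratio at 0–5 minutes. It could reflect relatedness across that whole radius, or only the neighbour excess already seen in the first analysis, counted a second time. The stated purpose, close versus distant contacts, needs these two to be separable.

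**Working it through.** **The plan's own figures.** No figure is stated for the travel-time bands, so the inputs were checked against the Genomic relatedness paragraph under Sample size.
- Interval around 10% of 250: 0.10 ± 1.96 × √(0.10 × 0.90 / 250) = 0.10 ± 0.037, or 6.3–13.7%, as stated.
- Two-sided 5% normal-approximation power (pooled variance under the null): 10% of 250 vs 60% of 35, over 99.9%; 10% of 250 vs 30% of 75, 97.4%; 60% of 35 vs 30% of 75, 85.5%. These agree with the stated >95%, >95% and >80%.

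**Inputs from the plan.** 250 Index cases, 35 household contact cases, 75 neighbourhood cases. 10% of Index cases match another Index case (stated as a maximum). The neighbourhood value is 30%, from "30% or less of Index case/neighbourhood case pairs are genomically".

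**Assumptions not in the plan.** Index matches occur in twos. Contact cases are spread at random over the 250 clusters. All five-house pairs lie within 5 minutes. A share f of different-neighbourhood pairs, varied from 1% to 30%, also lies within 5 minutes.

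**Pair counts.**
- Cases: 250 + 35 + 75 = 360. All pairs: 360 × 359 / 2 = 64,620.
- Household pairs: 35 + 35²/500 = 37.45.
- Five-house pairs: 75 + 35 × 75/250 + 75²/500 = 75 + 10.5 + 11.25 = 96.75.
- Different-neighbourhood pairs: 64,620 − 37.45 − 96.75 = 64,485.8.

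**Background per pair.** Index pairs: 250 × 249 / 2 = 31,125. 25 matched Index cases in twos make 12.5 matched pairs. 12.5 / 31,125 = 0.0402%.

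**Scenario: nothing is raised beyond the five houses.** Five-house pairs match at 30%; every other non-household pair matches at background.

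Band proportion p = (96.75 × 0.30 + 64,485.8 × f × 0.000402) / (96.75 + 64,485.8 × f)

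Odds ratio = [p / (1 − p)] / [0.000402 / (1 − 0.000402)]

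For f = 1%: p = (29.02 + 0.26) / 741.6 = 3.95%, odds ratio 102.

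| f (assumed) | Different-neighbourhood pairs in band | p, 0–5 min | OR, 0–5 vs 5+ min | Five-house share of band pairs | Five-house share of band matches |
|---|---|---|---|---|---|
| 1% | 645 | 3.95% | 102 | 13% | 99% |
| 5% | 3,224 | 0.91% | 23 | 2.9% | 96% |
| 10% | 6,449 | 0.48% | 12 | 1.5% | 92% |
| 20% | 12,897 | 0.26% | 6.6 | 0.7% | 85% |
| 30% | 19,346 | 0.19% | 4.7 | 0.5% | 79% |

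In the same scenario the 5–10, 10–20 and 20+ bands all sit at 0.04%, so their odds ratios against one another are 1.0. With five-house pairs taken out, the 0–5-minute odds ratio is also 1.0.

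**Sensitivity** (f from 1% to 30%).
- Five-house relatedness 15% instead of 30%: 51 down to 2.9.
- Background 2%, five-house 30%: 2.9 down to 1.07.
- Background 10%, five-house 30%: 1.3 down to 1.01.
- The 30% applied only to the 75 Index/neighbour pairs, with 580 to 42,561 different-neighbourhood pairs in the band (about 0.9% to 66%): 86 down to 2.3. At 10% instead of 30%: 29 down to 1.4.

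**The case against.** The strongest reply is that the first classification already reports neighbourhood pairs on their own, so an excess confined to them would be visible. Their counts could then be subtracted from the 0–5-minute band. That is true of the data, and it is why the remedy is cheap. But the article lists the categories of both analyses and names no such step, and neither analysis as listed makes the contrast.

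A second reply is that the size rests on quantities the plan does not give: the share of other pairs within 5 minutes, the background per pair, and how Index matches cluster. The 30% comes from a conditional power statement and is not a forecast. Larger Index clusters would mean more matched pairs, a higher background and a smaller odds ratio. Only the 'identical' level can be worked from the plan's figures, and the effect fades quickly as background rises. All of this stands and limits what can be said about size.

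A third reply is that a drop to pure background at the sixth house is extreme, and that any band averages over its contents. Under smoother decay, a raised 0–5-minute odds ratio would be a fair though coarse description. This also stands. The difficulty is that the planned output would not show which case applies.

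Three stronger readings might be inferred and are not supported.
- That the pooling creates a gradient over travel time. It creates one step at 5 minutes; a decline across 5–10, 10–20 and 20+ minutes could not come from it, so those bands remain informative.
- That the band mixes screened neighbours with unscreened residents. The other nearby pairs also include actively screened contacts of other Index cases.
- That the programme would be led to target a 5-minute radius. No passage ties a decision to that radius or says the travel-time result will be read alone. The Discussion refers to genomic match within neighbourhoods, which the first analysis addresses directly.

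**Conclusion.** The point holds in a limited form. The travel-time analysis cannot resolve what happens inside 0–5 minutes, and the first analysis does not supply the missing contrast. Under the plan's 10% and 30% figures at the 'identical' level, an effect confined to the five houses would give a 0–5-minute odds ratio of roughly 100 down to 5. The five-house pairs, at most 13% of the band, would supply 79–99% of its matches. This rests on Index matches in twos and an assumed 1–30% of different-neighbourhood pairs in the band. With lower neighbour relatedness, a larger nearby share or a higher background the effect is smaller, and at the wide SNP levels it may be negligible. This is an inexpensive improvement to a stated classification; it does not invalidate the genomic analysis or the comparisons between later bands.

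**What to change.** In the travel-time analysis, split the 0–5-minute band into same-neighbourhood and different-neighbourhood pairs. This gives six categories: household; same five-house neighbourhood; and different-neighbourhood pairs at 0–5, 5–10, 10–20 and 20 or more minutes. Repeating the travel-time analysis on different-neighbourhood pairs only would also serve for the distance pattern.

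Read that pattern from the four different-neighbourhood categories, and report same-neighbourhood pairs against 0–5-minute different-neighbourhood pairs as the check on whether an excess is local to the five houses.

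The cost is a sentence or two of analysis text and one extra category. Household coordinates are already collected, and neighbourhood membership is already needed for the first classification.
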